## Abstract

**Background:**

Diabetic kidney disease (DKD) is a major microvascular complication of diabetes mellitus and the primary cause of end-stage renal disease. Existing therapies for DKD are not sufficiently effective. We report the protocol of a pragmatic randomized controlled trial of the use of traditional Chinese herbal medicine to treat patients with DKD.

**Methods/design:**

This will be a multicenter randomized controlled trial. A total of 266 patients with DKD (106 with early stage, 80 with middle-stage, and 80 with advanced-stage disease) with an estimated glomerular filtration rate (eGFR) ≥ 30 mL/min/1.73m^2^will be included. Participants with DKD of each stage will be randomly allocated at a 1:1 ratio to either the experimental group, which will receive *Xiaozhen* formula and basic treatment, or the control group, which will receive basic treatment only. The study duration will be 24 weeks. The primary outcome will be urinary microalbumin excretion rate for early stage DKD, 24-h urinary protein for middle-stage DKD, and eGFR for advanced-stage DKD. Adverse events will also be evaluated. Data for all outcome indicators will be collected at baseline and weeks 4, 12, and 24.

**Discussion:**

This study will provide evidence of the effectiveness and safety of traditional Chinese herbal medicine in treating patients with DKD.

**Trial registration:**

Chinese Clinical Trials Registry: ChiCTR-IOR-16010072. Registered on 2 December 2016.

**Electronic supplementary material:**

The online version of this article (10.1186/s13063-018-2749-6) contains supplementary material, which is available to authorized users.

## Background

Diabetic kidney disease (DKD) is a major microvascular complication of diabetes mellitus (DM).With the prevalence of diabetes increasing, the incidence of DKD is growing rapidly, not only in the Western world but also in some developing countries. Thus, the number of patients with chronic kidney disease (CKD) related to DM in China, recently estimated to be 24.3 million, has exceeded the number of patients with CKD related to glomerulonephritis [1]. DKD is associated with an extremely high risk of progression to end-stage renal disease (ESRD) and cardiovascular morbidity and mortality [2, 3], emphasizing the importance of early prevention and treatment. However, few effective therapies are currently available. In addition to glycemic control, renin-angiotensin-aldosterone system (RAAS) inhibition has remained the mainstay of the treatment for DKD for a long time. Many experimental studies and clinical trials have demonstrated that RAAS inhibition with angiotensin-converting-enzyme inhibitors (ACEIs) or angiotensin receptor blockers (ARBs) can reduce microalbuminuria and improve renal function, slowing the progression to ESRD [4–6]. However, many adverse effects of ACEIs and ARBs, such as hyperkalemia [7], acute kidney injury [8], rhinitis, persistent cough, and angioedema [9, 10], preclude the continuous use of this therapy in many cases. Moreover, patients with a low estimated glomerular filtration rate (eGFR) usually cannot receive RAAS inhibitors. Although new therapies have been tried in the recent years, few have been proven to be both effective and safe [11–13].

In China, many patients with CKD resort to traditional Chinese herbal medicine (TCHM).Many in vitro and animal studies have demonstrated the biological activity and therapeutic effects of TCHM [14, 15]. However, substantial variations in TCHM individual treatment patterns and the need for frequent adjustments make it difficult to design a strict modern controlled trial for traditional Chinese therapy. Hence, high-quality randomized controlled trials, and especially well-designed clinical trials, of traditional Chinese medicine (TCM) are rare.

The *zhenjia* theory is first mentioned in the *Inner Canon of the Yellow Emperor* (*Huang di Nei jing*). *Zhenjia* refers to a complex of phlegm, stasis, heat, and damp that mainly forms and exists in collaterals. In CKD, *zhenjia* forms in the collaterals of the kidney and exacerbates kidney injury. TCHM can help dissolve *zhenjia*. Our previous studies have shown that a formula based on the *zhenjia* theory can decrease urinary albumin and serum creatinine (Scr) levels and suppress interstitial expansion and glomerulosclerosis in rats with DKD. These therapeutic effects might be related, at least partially, to the inhibition of inflammatory response and extracellular matrix accumulation mediated by the TNF-α/NF-κBp65 signaling pathway [16]. According to the *zhenjia* theory, the composition of *zhenjia* is different in different stages of DKD. Thus, *zhenjia* is mainly composed of heat, stasis, and turbidity toxin in the early, middle-, and advanced-DKD stages, respectively. Therefore, it is necessary to dissipate the heat, remove the blood stasis, and dislodge the turbid toxin. Accordingly, we prescribe different formulas to patients with DKD of different stages. The *Tourexiaozhen* formula is prescribed to patients with early stage DKD to dissipate heat; the *Huoxuexiaozhen* formula is utilized for middle-stage DKD to remove blood stasis; while the *Xiezhuoxiaozhen* formula is employed for advanced-stage DKD to dislodge the turbid toxin. The proposed study will be designed as a randomized controlled trial that evaluates DKD treatment according to the disease stages. In order to recapitulate the real-world practice of TCM, it will be possible to adjust each formula individually according to the patient’s signs and symptoms.

## Methods/design

### Study design

The proposed study is a prospective, multicenter, assessor- and analyst-blinded, pragmatic randomized controlled trial. A total of 266 participants will be recruited at the following six tertiary A hospitals of TCM in Beijing: Dongzhimen Hospital Affiliated to Beijing University of Chinese Medicine, Guang’anmen Hospital, China Academy of Chinese Medical Sciences, Beijing Hospital of Traditional Chinese Medicine, Wangjing Hospital, China Academy of Chinese Medical Sciences, Xiyuan Hospital, China Academy of Chinese Medical Sciences, Beijing Hospital of Integrated Traditional Chinese and Western Medicine, and Fangshan Traditional Medical Hospital of Beijing. Eligible patients who agree to participate will be randomly allocated at a 1:1 ratio to either the experimental group or the control group according to disease stage. After randomization, patients in the experimental group will receive basic treatment and TCHM, whereas patients in the control group will receive basic treatment only. The treatment will continue for 24weeks in both groups. Four visits will be scheduled for each patient: weeks 0 (baseline), 4, 12, and 24. The study flowchart is shown in Fig. 1. The Standard Protocol Items: Recommendations for Interventional Trials (SPIRIT) Checklist is presented in Additional file 1.

**Fig. 1 Fig1:**
[figure not shown]
Study flowchart. Group C: control group. Group E: experimental group

### Participants

#### Diagnostic criteria

The diagnostic criteria of this trial will be set based on the National Kidney Foundation Kidney Disease Outcomes Quality Initiative (NKF-KDOQI) guidelines [17], the Kidney Disease Improving Global Outcomes (KDIGO) 2012 Clinical Practice Guideline for the Evaluation and Management of Chronic Kidney Disease [18], and the Consensus for Prevention and Treatment of Diabetic Kidney Disease 2014 of Chinese Diabetes Society [19]. For a diagnosis of DKD, patients with DM will have to have at least one of the following conditions:Albuminuria (for microalbuminuria, out of three tests, two repeated tests performed within 3–6 months will need to produce abnormal results)Diabetic retinopathy with CKDDKD confirmed by renal biopsy

#### Stage differentiation

Early stage DKD: urinary microalbumin excretion rate (UAER) of 30–300 mg/24 h or urinary albumin-to-creatinine ratio (ACR) of 30–300 mg/g (mg/mmol)Middle-stage DKD: UAER > 300 mg/24 h or ACR > 300 mg/g (mg/mmol), or 24-h urinary protein (24-h UP) > 0.5 g and eGFR ≥ 60 mL/min/1.73m^2^Advanced-stage DKD: eGFR of 30–60 mL/min/1.73m^2^

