### Randomization and blinding

The random sequence will be generated by the Center for Evidence-Based Medicine of Beijing University of Chinese Medicine using Statistical Analysis System (SAS version 9.2), and randomization will be stratified according to study center and DKD stage. Eligible patients with DKD of each stage will be randomized to the experimental group or the control group at a 1:1 ratio. The group numbers will be provided in envelopes made from carbonless paper. At each center, the envelopes will be kept by a study administrator who will not directly participate in the recruitment or follow-up of any participant, and the group numbers will be subsequently disclosed. The administrator will open one envelope and provide the participant with their group number on the day of inclusion.

Different people will serve as investigators, therapists, and assessors. Assessors of primary and secondary endpoints and data analysts will be blinded to the treatment allocation throughout the course of the study, while patients, investigators, and therapists administering the treatment will not be blinded.

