
### Outcomes

#### Primary outcomes

For early stage DKD, the primary outcome will be UAER. For middle-and advanced-stage DKD, the primary outcomes will be 24-h UP and eGFR, respectively.

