#### Laboratory tests

Routine laboratory tests (CBC and general urine analysis, Scr, BUN, AST, ALT, ALP, GGT, UAER, 24-h UP, and HbA1c) will be performed by the clinical laboratory of each center. For CRP, IL-6, and TNF-a level determination, an additional 3–5 mL of venous blood will be collected. The serum will be separated by centrifugation for 15 min at 3000×g, aliquoted, labeled concisely, and stored at − 80 °C until the final analysis. Repeated freeze-thaw cycles will be avoided. The inflammation indicators will be measured at the Research Center, Dongzhimen Hospital Affiliated to Beijing University of Chinese Medicine using specific ELISA kits.

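### The ACR staging limits carry the same numbers for mg/g and mg/mmol, units that differ about 8.84-fold, so a patient staged on ACR alone could fall in either of two stages

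*Protocol article*

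**What the plan says.** Under Stage differentiation, early stage can be met on a 24-hour excretion rate or on a ratio: "urinary microalbumin excretion rate (UAER) of 30–300 mg/24 h or urinary albumin-to-creatinine ratio (ACR"), the ratio limits being printed as "urinary albumin-to-creatinine ratio (ACR) of 30–300 mg/g (mg/mmol"). Middle stage starts with "UAER > 300 mg/24 h or ACR > 300 mg/g (mg/mmol"), with 24-h urinary protein above 0.5 g as a further alternative. Both ratio limits are followed by mg/g and then mg/mmol in brackets. No converted values are given, and nothing says which unit governs. Advanced stage does not use the ratio: "Advanced-stage DKD: eGFR of 30–60 mL/min/1.73m^2".

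Stage then decides three things:

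- **Stratum.** Under Randomization and blinding, "randomization will be stratified according to study center and DKD stage".
- **Formula.** The Experimental group section assigns a different formula to each stage.
- **Primary outcome.** "For early stage DKD, the primary outcome will be UAER"; for middle stage it is 24-h urinary protein, and for advanced stage eGFR.

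Of the routine tests, the Laboratory tests section says that they "will be performed by the clinical laboratory of each center". Its list includes UAER and 24-h urinary protein but not ACR.

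**The concern.** The bracketed unit reads as if mg/g and mg/mmol were interchangeable. One is albumin per gram of creatinine and the other albumin per millimole, so the same number means a very different degree of albuminuria in each. The form appears at both ratio limits, and whichever unit was intended, the printed limits are wrong for the other.

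The rule matters because stage is the hinge of this design. If a patient is staged on ACR alone, and the printed numbers are applied in the unit that was not intended, that patient could be randomised in the wrong stratum, given the formula meant for another stage, and analysed on another stage's primary outcome. The fault is separate from any overlap between the stage definitions: a precedence rule or an extra eGFR limit would leave the false ratio limit in place.

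**Working it through.** **Inputs.** From Stage differentiation: ACR 30–300 (early) and > 300 (middle), each labelled mg/g and mg/mmol. Not in the document: the molar mass of creatinine, M = 113.12 g/mol, assumed as a physical constant.

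**Conversion.** One mmol of creatinine weighs M/1000 g, so 1 mg/mmol = 1000/M mg/g = 1000/113.12 = 8.84 mg/g, and 1 mg/g = 0.11312 mg/mmol. Rounding M to 113 gives 1000/113 = 8.85, so the result does not hang on the decimals. The same numbers could serve both units only if 1000/M were 1, that is, if M were 1000 g/mol.

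**The limits in each unit.**

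- 30 mg/g × 0.11312 = 3.39 mg/mmol; 300 mg/g × 0.11312 = 33.9 mg/mmol.
- 30 mg/mmol × 8.84 = 265 mg/g; 300 mg/mmol × 8.8402 = 2652 mg/g.

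The printed equality therefore cannot be reproduced.

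**Stage by ACR alone under each printed unit.**

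| ACR in mg/g | same value in mg/mmol | limits read as mg/g | limits read as mg/mmol |
|---|---|---|---|
| below 30 | below 3.4 | below early range | below early range |
| 30 to below 265 | 3.4 to below 30 | early | below early range |
| 265 to 300 | 30 to 33.9 | early | early |
| above 300, up to 2652 | above 33.9, up to 300 | middle | early |
| above 2652 | above 300 | middle | middle |

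Two examples. An ACR of 884 mg/g is 884 × 0.11312 = 100 mg/mmol: middle stage in the first unit, early in the second. An ACR of 100 mg/g is 11.3 mg/mmol: early in the first unit, below the early range in the second.

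**Effect on the sample size: none.** The formula under Sample size, with its own rounded z values, uses (1.64 + 1.28)² = 8.5264.

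- Early: 8.5264 × (51² + 27²)/(70 − 44)² = 8.5264 × 3330/676 = 42.0, so 42; 42/0.8 = 52.5, so 53.
- Middle: 8.5264 × (1.09² + 0.95²)/(3.25 − 2.50)² = 8.5264 × 2.0906/0.5625 = 31.7, so 32; 32/0.8 = 40.
- Advanced: 8.5264 × (9.1² + 10.2²)/(40.5 − 33.4)² = 8.5264 × 186.85/50.41 = 31.6, so 32; 32/0.8 = 40.

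The total is 2 × (53 + 40 + 40) = 266, as stated. No ACR limit enters this calculation.

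**The case against.** The strongest reply is that the slip may never touch a patient. ACR is not in the routine list under Laboratory tests or in the Fig. 2 caption, and it is not an outcome. The scheduled urine albumin and protein measures are the 24-hour ones, where the conflict does not arise. No centre is shown to report mg/mmol. Many readers would take mg/g as the governing unit, since it comes first and its numbers match the neighbouring UAER limits; the bracket may be a conversion whose figures were left out. The Abstract has all outcome indicators measured at baseline, so an early-stage patient with a UAER far above 300 mg/24 h would be noticed.

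Most of this stands as a limit on the consequences. It shows that misstaging is possible rather than demonstrated, and that local testing alone is not evidence of mixed ACR units. It does not rescue the text. ACR remains a sufficient criterion for early and for middle stage, and the alternatives are joined by *or* without precedence, so a UAER result does not formally override an ACR stage. The baseline UAER can also expose an error only in patients who were enrolled; it cannot do so for someone passed over because the ACR seemed too low. Which unit was meant is for the sponsor to say.

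One part of the worry belongs elsewhere. A patient whose UAER and ACR disagree can meet both the early and the middle definition even when a single correct unit is used. That is a matter of overlapping definitions, not of units.

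**Conclusion.** The ACR limits are wrong as written: whichever unit was meant, the other is out by a factor of 8.84. By ACR alone, values above 300 and up to 2652 mg/g change between middle and early stage with the unit, and values from 30 to below 265 mg/g change between early stage and below the range. The conclusion rests only on the printed text and the molar mass of creatinine. It affects the early/middle boundary and the lower limit of early stage; the definition of advanced stage and the total of 266 are untouched.

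Three stronger readings are not supported:

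- A reader might infer that the early-stage UAER comparison would lose much of its power through heavily albuminuric patients placed there by mistake. The article gives neither a misstaging rate nor the UAER values of such patients, so any figure would be invented. The Statistical analysis section also allows the Mann-Whitney test, which is far less sensitive to a few extreme values than the *t* test.
- A reader might infer that most of the intended early-stage patients would be lost. The shift from 30–300 to 265–2652 mg/g describes the width of an interval, not a share of patients, and UAER 30–300 mg/24 h still qualifies a patient.
- A reader might infer that the unit decides eligibility. Stage is not a listed inclusion criterion, and the diagnostic criteria for DKD set no ACR number. Stage governs stratum, formula and primary outcome.

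This is a false limit in a rule that assigns patients, with a possible but undemonstrated effect. It should be corrected because correction is cheap and, by the Trial status section, recruitment is under way.

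**What to change.** 1. The sponsor confirms which unit is meant.
2. Both ACR limits under Stage differentiation are reconciled: stated in that unit, with arithmetically correct equivalents in the other. If mg/g is meant, 30–300 mg/g is 3.4–33.9 mg/mmol and > 300 mg/g is > 33.9 mg/mmol. If mg/mmol is meant, 30–300 mg/mmol is 265–2652 mg/g and > 300 mg/mmol is > 2652 mg/g.
3. The CRF records the ACR unit beside the value wherever ACR is used for staging.
4. The stage of any patient already enrolled on ACR alone is checked against the confirmed limits.

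The cost is a one-line correction to the protocol, one CRF field and a query to centres. No extra patients, visits or tests are needed, and the sample size does not change.

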#### Inclusion criteria

Presence of DKD according to the above diagnostic criteriaAge between 25 and 75 yearseGFR ≥ 30 mL/min/1.73m^2^ without dialysisFor those with hypertension, controlled blood pressure ≤ 140/90 mmHg; for the elderly, systolic blood pressure (SBP) ≤ 150 mmHgGlycated hemoglobin (HbA1c) level ≤ 7%; for those with repeated hypoglycemia, severe microvascular or macrovascular complications, other severe comorbidities, or difficulties in achieving the standard requirements in spite of adequate therapy, HbA1c ≤ 8%Signed informed consent

#### Exclusion criteria

Severe infection, anemia, electrolyte imbalance, or acute complications of DM in the previous 4 weeksSevere cardiac, cerebral, hepatic, or hemorrhagic diseases, including cerebral infarction, cerebral hemorrhage, transient ischemic attack, myocardial infarction, unstable angina, heart failure, and hepatic inadequacy with aspartate transaminase (AST) or alanine aminotransferase (ALT) levels more than twice the normal upper limitUse of corticosteroids or immunosuppressants in the previous 3 monthsOliguria, anuria, severe edema, massive pleural or peritoneal effusionRenal transplantationMental disordersPregnancy or lactationAllergy to the trial drugsParticipation in other clinical studiesIncomplete understanding of the study, refusal to participate, or lack of signed informed consent

#### Handling of withdrawal and dropout

Participants will be able to withdraw from the study for any reason at any time, and the reason will be recorded faithfully in the case report form (CRF). Investigators can also remove participants from the study to ensure their safety or maintain the quality of the trial. Participants with any of the following conditions may be removed from the study:Occurrence of diseases or conditions mentioned in the exclusion criteria during the course of the studyOccurrence of severe complications and/or general health deteriorationOccurrence of serious adverse events (SAEs)Rapidly increasing Scr level (more than 50% of baseline) or ESRDViolation of the study protocolVoluntary withdrawal from the trial or loss to follow-up

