### Adverse event (AE) reporting

AEs will be defined as undesirable, unexpected symptoms, signs, or diseases regardless of whether related to the treatment. If any AE happens, the investigators will take proper measures (dose adjustment, drug withdrawal, or symptomatic treatment) to ensure safety of the participant and perform continuous follow-up until the patient’s condition returns to normal. The relationship between the AEs and the experimental treatment will be further evaluated. All AEs and their characteristics, including the manifestation, onset date and time, duration, cause, relationship with the experimental treatment, specific therapy, and outcome, will be recorded.

In case of a severe AE (SAE) that can result in death, disability, hospitalization, or prolonged hospitalization, in addition to the above-mentioned measures, the chief investigator will be notified immediately and a written report will be submitted to the Research Ethics Committee within 24 h.

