### Statistical analysis

Statistical analysis will be conducted at the Center for Evidence-Based Medicine of Beijing University of Chinese Medicine using Statistic Package for Social Science (SPSS, version 22.0, Beijing University of Chinese Medicine). Intention-to-treat and per protocol sets will be used to analyze the efficacy of TCHM. A safety analysis set will be used to evaluate the safety of the trial. Missing outcome variables will be estimated using the principle of the last observation carried forward, with the data from the last study follow-up used as the final results.

The independent-samples *t* test or Mann-Whitney test will be used for comparison of the trial primary outcomes between the two groups, including UAER in the early stage subgroup, 24-h UP in the middle-stage subgroup, and eGFR in the advanced-stage subgroup, which are all continuous variables with four measurements. Moreover, repeated measures analysis of variance will be attempted to further test the time effect and treatment cross-effect. With regard to the secondary outcomes, the independent-samples *t* test or Mann-Whitney test will be used to analyze continuous variables, and the chi-squared test will be used to analyze classified variables. With regard to safety outcomes, the incidence of AEs will be determined and a comparison between the two groups will be attempted. A stratified analysis of data according to DKD stage or center will be attempted in order to decrease bias. A *P* value < 0.05 will be considered to indicate a statistically significant difference.

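### Participants may be removed from the study for reasons tied to outcome, harm or adherence, and no outcome measurement is provided for afterwards, which weakens the intention-to-treat analysis

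*Protocol article*

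**What the plan says.** Under Handling of withdrawal and dropout, the protocol article says: "Investigators can also remove participants from the study to ensure their safety or maintain the quality of the trial". A list follows, introduced by "Participants with any of the following conditions may be removed from the study". It covers new exclusion conditions, severe complications or general deterioration, serious adverse events, a rapid Scr rise of more than 50% of baseline or end-stage renal disease, violation of the protocol, and voluntary withdrawal or loss to follow-up. The list applies to both arms.

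Under Randomization and blinding, assessors and analysts are blinded, "while patients, investigators, and therapists administering the treatment will not be blinded".

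Under Primary outcomes: "For middle-and advanced-stage DKD, the primary outcomes will be 24-h UP and eGFR, respectively". The early stage uses the urinary microalbumin excretion rate (UAER).

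Under Statistical analysis: "Intention-to-treat and per protocol sets will be used to analyze the efficacy of TCHM", and "Missing outcome variables will be estimated using the principle of the last observation carried forward", with the data from the last follow-up serving as the final result.

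Under Adverse event (AE) reporting, investigators may adjust the dose, withdraw the drug or treat symptoms, and are to "perform continuous follow-up until the" condition is normal again. Data collection schedules visits at baseline and weeks 4, 12 and 24.

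**The concern.** An intention-to-treat comparison at week 24 relies on outcomes being measured in everyone randomized, whatever happens to their treatment. Here several grounds for leaving the study are themselves consequences of the disease course, of harm or of non-adherence. One of them, the Scr rise, drives the advanced-stage primary outcome directly, because eGFR is calculated from Scr. Another, protocol violation, already has its proper place in the per-protocol set.

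If removal ends measurement, week-24 values are lost selectively. Since unblinded staff decide at their discretion, the loss can differ between arms for reasons related to allocation, and randomization no longer fully protects the comparison. Controls receive basic treatment only and have no study formula to stop, so removing a control from the study mainly removes that patient's outcome.

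**Working it through.** **1. The plan's own figure.** From Sample size, with the rounded normal quantiles used there, (1.64 + 1.28)² = 8.53:
- Early: 8.53 × (51² + 27²)/26² = 42.0; 42/0.8 = 52.5, so 53 per arm.
- Middle: 8.53 × (1.09² + 0.95²)/0.75² = 31.7, so 32; 32/0.8 = 40 per arm.
- Advanced: 8.53 × (9.1² + 10.2²)/7.1² = 31.6, so 32; 32/0.8 = 40 per arm.
- Total: 2 × (53 + 40 + 40) = 266.

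These reproduce and are not disputed. The 20% allowance restores numbers only: 32 advanced-stage completers per arm give the planned 90% power (one-sided 5%) if loss is unrelated to outcome. It does not correct selective loss.

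**2. How closely the trigger tracks the outcome.** The article gives no eGFR equation. Assume eGFR varies as Scr to a power between −1 and −1.2, other factors fixed. For Scr at 1.5 times baseline:
- power −1: 1 − 1.5^(−1) = 33% fall;
- power −1.2: 1 − 1.5^(−1.2) = 39% fall.

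A patient starting at 45 becomes removable at about 28–30. Over the entry range ("Advanced-stage DKD: eGFR of 30–60 mL/min/1.73m"²), the point is about 18–20 for a start of 30 and about 37–40 for a start of 60. This direct link holds only in the advanced stage: 80 of 266 patients, or 30%. In the other two stages Scr is a secondary outcome.

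**3. What carrying forward preserves.** This depends on when the trigger is seen:

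| Trigger first seen | Value carried to week 24 | Not counted |
|---|---|---|
| At week 4 | Week 4, if that value is kept | Change over 20 weeks |
| At week 12 | Week 12, if that value is kept | Change over 12 weeks |
| Between visits | Previous visit, possibly before the fall | The fall itself and anything after |
| At week 24 | Week 24 | Nothing |

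Removal for a serious adverse event, deterioration or protocol violation follows the same pattern in all three stages, whichever primary outcome applies.

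**4. Possible size (hypothetical).** Let p be the proportion removed in an arm and d the average further eGFR decline by week 24 that is not counted. Carrying forward overstates that arm's mean by p × d, so the experimental-minus-control difference shifts by

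p_E × d_E − p_C × d_C.

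None of these quantities is in the article. Assume d = 7 mL/min/1.73m² in both arms, about the planned effect of 40.5 − 33.4 = 7.1:

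| Imbalance in removal | Patients, of 40 per arm | Shift if more controls are removed | Shift if more experimental patients are removed |
|---|---|---|---|
| 5 points | 2 | −0.35 | +0.35 |
| 10 points | 4 | −0.7 | +0.7 |
| 20 points | 8 | −1.4 | +1.4 |

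The 10-point row is 0.7/7.1 = 10% of the planned effect. More removals among controls shrink a true benefit; more among experimental patients inflate the apparent benefit and can hide renal harm. With equal p and d the shift is zero.

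**The case against.** Several counterarguments have force.

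- **The article never says that data collection stops on removal.** A reader might infer that it does, but the section is silent and the article condenses a fuller protocol. What stands is that the text speaks of leaving the study, provides only event follow-up afterwards, and supplies an imputation rule for the missing outcomes.
- **Intention-to-treat is not defeated.** Carrying forward keeps removed patients in the set. The analysis is weakened through replaced values, not through exclusion.
- **The worst outcomes are not necessarily unmeasured.** Scr must be measured to meet the trigger, and laboratory tests are done at each visit. The triggering eGFR may itself be the value carried forward, leaving only later change uncounted.
- **Stopping the drug and leaving the study are not wholly merged.** The adverse event section allows drug withdrawal with continued follow-up. That follow-up runs until recovery, however, and does not promise a week-24 outcome.
- **Discretion is limited.** Removal is optional and tied to safety or trial quality. Quality assurance and data management requires withdrawals to be explained in the case report form and has the monitor check the withdrawal criteria. This restrains differential removal but recovers no missing outcomes.
- **Telephone follow-up is mentioned in the Discussion.** It is aimed at compliance, and a call cannot yield eGFR or urinary protein.
- **Some exits are legitimate.** Voluntary withdrawal and loss to follow-up belong in any such list.

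**Conclusion.** The concern holds in a limited form. As written, the plan lets unblinded investigators take patients out of the study for reasons related to outcome, harm or adherence, and does not provide for measuring outcomes afterwards. Carrying forward then represents those patients by an earlier value, so change after their last visit is not counted.

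How often this would happen, in which arm, and with what effect cannot be derived from the article. The figure of 0.7 mL/min/1.73m² and its range show scale only: they rest on assumed removal imbalances and an assumed further decline. A simulation would not settle the size, because the baseline distribution, the correlation over time and the frequency of removal would all have to be assumed. A reader might infer that the rule favours the herbal arm; the documents do not support any fixed direction.

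This is an inexpensive improvement to the protocol wording, not evidence that the primary analyses are invalid. It is best made now: the article reports that recruitment is under way, and outcomes left unmeasured cannot be recovered by later analysis.

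**What to change.** Leave the clinical criteria and treatment decisions in Handling of withdrawal and dropout unchanged. Add that meeting a criterion does not end outcome collection. Suggested wording: *Unless consent for follow-up is withdrawn, all randomized participants keep the scheduled week 4, 12 and 24 visits, the primary outcome for their stage is measured, and the observed values enter the intention-to-treat analysis.*

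State also that protocol violation is a reason for exclusion from the per-protocol set only, not for removal from the study.

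The sample size does not change and no new visit dates are needed, since the visits already stand in Data collection. The cost is an amendment and a few more visits for patients who have stopped treatment or would otherwise have been removed.
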